#### Recruitment {15}

Figure 1 shows the participant flow chart throughout the trial. Social media will be used in the recruitment of participants, which is planned to take 18 months, beginning in May 2022. Recruitment will also be carried out at Shanghai Sixth People’s Hospital, Shanghai Jiao Tong University, Shanghai, China. For those who are interested in the trial, a face-to-face interview will be scheduled by an experienced researcher. The subjects and their guardians will be informed about the study’s purpose, techniques, advantages, and any discomfort or risks. If they understand the information, they will sign the informed consent form.

## Assignment of interventions: allocation

### Sequence generation {16a}

Participants will undergo randomization, being assigned to either the LIPUS group or the sham group in a 1:1 ratio, facilitated by a computer-generated randomization sequence. To safeguard the impartiality and autonomy of the allocation data, research assistants who are not engaged in outcome assessment will be responsible for generating sequentially numbered opaque sealed envelopes according to the randomization list.

### Concealment mechanism {16b}

These envelopes will be used to maintain the confidentiality and independence of the allocation process. When necessary, the designated assistant will unseal the envelopes and oversee the coordination of therapeutic interventions.

### Implementation {16c}

The sealed envelopes will be opened and resealed during the initial stage by the staff in charge of randomization. Subsequently, the code will be communicated to the LIPUS experimenter.

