### Who will take informed consent? {26a}

The research assistant ([name]) will obtain informed consent from participants before conducting the baseline evaluation in the participant reception room. Participants will engage in a 30-min group discussion with a research assistant. This session will encompass an overview of the PD therapy protocol for the trial and detailed instructions on how to use the wearable LIPUS device. Participants will receive an explanation of the study’s purpose, their role in it, and the potential benefits and risks involved. Meanwhile, participants will also be provided with an instructional video, produced by the research team, demonstrating the correct usage of the LIPUS device. If participants have any questions, they are encouraged to ask, and they have the freedom to decide whether to participate in the study after fully comprehending the information provided.

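### The allocation procedure as written does not secure concealment: envelopes are opened and resealed, and the sections do not agree on who opens them or when

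*Protocol article*

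**What the plan says.** Three consecutive sections of the protocol article describe allocation.

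- Sequence generation {16a}: participants are randomised "in a 1:1 ratio, facilitated by a computer-generated randomization sequence". On preparing the envelopes, "research assistants who are not engaged in outcome assessment will be responsible for generating sequentially numbered opaque sealed envelopes according to the randomization list".
- Opening is described once under Concealment mechanism {16b}, as follows: "When necessary, the designated assistant will unseal the envelopes and oversee the coordination of therapeutic interventions".
- It is described again, in other terms, under Implementation {16c}, which says: "The sealed envelopes will be opened and resealed during the initial stage by the staff in charge of randomization". The next sentence reads: "Subsequently, the code will be communicated to the LIPUS experimenter".

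Two other sections bear on who meets candidates. Under Who will take informed consent? {26a}, one named research assistant "will obtain informed consent from participants before conducting the baseline evaluation in the participant reception room". Under Recruitment {15}, for people interested in the trial, "a face-to-face interview will be scheduled by an experienced researcher".

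**The concern.** A sealed-envelope scheme conceals allocation on two conditions: nobody who can influence enrolment sees the next assignment before the participant is committed, and an unbroken seal proves it. Opening and resealing as a planned step gives up the second condition. Depending on what the initial stage means, it may give up the first as well.

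Selection bias is what is at stake. Someone who knows the next assignment can defer, discourage or reorder candidates. Some entry criteria leave room for judgement, such as whether the temporal bone window is sufficient and whether the drug regimen is in principle unchanged. The trial has one site and 48 participants, so a few steered enrolments could matter. Blinding after assignment does not undo this, and analysis cannot reliably remove it. The article also plans no steering group, no data monitoring committee and no audit ({5d}, {21a}, {23}), so the envelope trail is one of the few checks available.

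**Working it through.** The point is procedural and the article gives no figure to reproduce. The check sets the sections side by side.

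**1. Who opens the envelopes, and when?** {16b} names a designated assistant, acting when the need arises, who also coordinates the interventions. {16c} names the staff in charge of randomisation, acting during an initial stage. These may be the same people, but nothing links the two accounts, and their timing differs.

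**2. What does the initial stage mean?** It is not defined, and two readings are possible.
- *Start of the trial.* All envelopes are opened and resealed before enrolment, and whoever does this sees the upcoming assignments.
- *Start of each participant's treatment.* One envelope is opened, the code is passed on, and the envelope is resealed. Nothing need be known in advance. However, a resealed envelope can no longer show whether it was first opened at the proper time.

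Tamper evidence is lost under both readings. Advance exposure follows only from the first.

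**3. Is opening tied to completed enrolment?** No section shown says that an envelope is opened only after consent, confirmed eligibility and the baseline UPDRS III. Table 1 has no randomisation row. The flow chart in Fig. 1 is not available here and may give the order, so the table's silence carries little weight alone.

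**4. Are the roles separated?** {16a} bars those who prepare the envelopes from outcome assessment only. These people work from the randomisation list and so have access to the sequence. Nothing bars them from consent or eligibility work. {26a} gives consent to a research assistant, and the article does not say whether that person is among those who prepare or open envelopes.

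**5. How large could the effect be?** The documents do not allow an estimate. The following is an illustration on assumed inputs. Let k better-prognosis candidates be steered into one arm and k worse-prognosis candidates into the other. Let their expected 4-month change differ by 5 points, with 48 / 2 = 24 participants per arm.
- Shift relative to an even split of those candidates: k × 5 / 24. For k = 2, 3 and 5 this is 0.42, 0.63 and 1.04 points.
- Swing between one fully steered allocation and its exact reverse: 2 × k × 5 / 24. For k = 2, 3 and 5 this is 0.83, 1.25 and 2.08 points.

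For k = 3 these are 0.625 / 5 = 12.5% and 1.25 / 5 = 25% of the 5-point difference that Sample size and power {14} treats as clinically meaningful. The first formula measures bias against fair randomisation; the second is an outer contrast. The number of candidates, the prognostic gap and the perfectly directional steering are all assumed.

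**The case against.** The strongest defence is that {16c} describes a step for each participant: open the envelope, give the code to the person who sets up the device, and reseal it so that others stay blind. The sentence about passing on the code fits this, as does the as-needed opening in {16b}. On that reading resealing serves blinding and no future assignment is revealed. The envelope may also hold only a code, since Procedure for unblinding {17b} keeps the group identities undisclosed until the analysis is finished. This stands as a plausible reading, but it does not restore tamper evidence, and the article does not state it.

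A reader might infer that the staff who take consent are the staff who open the envelopes. The article does not support this. {16c} names the staff in charge of randomisation, not research assistants, and a shared job title does not show a shared person. If the consenting assistant also conducts the baseline evaluation, as {26a} can be read, the restriction in {16a} may even bar that person from preparing envelopes. What remains is that no separation is stated.

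A reader might also infer that allocation was known before the baseline score was taken. Who will be blinded {17a} keeps outcome assessors and clinic staff unaware of assignment, so the text does not put that knowledge with the person scoring UPDRS III.

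Finally, an article condenses a fuller protocol, and mere silence in it would not be a finding. The open-and-reseal step, however, is stated, not omitted.

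**Conclusion.** The point holds in limited form. The procedure as written does not secure concealment, for three reasons: a planned reseal removes tamper evidence, {16b} and {16c} give different accounts of opening, and those who prepare the envelopes are separated from outcome assessment but not from consent or eligibility.

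That upcoming allocations were known, or that concealment was in fact lost, is not shown. Both would require the start-of-trial reading of {16c}, and steering would further require that the knowledge reached someone able to influence enrolment. No size of bias can be attached to the finding. The figures above show only what deliberate steering could do under assumed inputs, and the conclusion does not depend on them.

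**What to change.** Delete the open-and-reseal step and rewrite {16a} to {16c} as one consistent procedure:

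- Order of events: signed consent, eligibility confirmed, baseline assessments including UPDRS III completed, participant identifier and date written on the next numbered envelope, envelope opened once, device issued.
- Staff who generate the list, prepare envelopes or open them have no role in consent, eligibility or baseline assessment.
- Opened envelopes are kept, dated, as an audit trail. If resealing was meant to protect blinding, store them with restricted access instead.

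Trial status gives recruitment as May 2022 to November 2023, so enrolment may already be complete. In that case the trial report should state who opened the envelopes, when this was done relative to consent and baseline, and whether any were opened before their participant was enrolled.

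The cost is wording and, if enrolment is still open, a reassignment of tasks among existing staff. No extra visits or participants are needed.

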## Assignment of interventions: blinding

### Who will be blinded {17a}

Both patients and clinic staff members, including caregivers, outcome assessors, and statistical analysts, will be kept unaware of the group assignments. The distinction between whether the intervention involves LIPUS or null stimulation will not be disclosed at any point during the study. Clinicians [name], [name], and [name] have access to the final trial dataset.

### Procedure for unblinding if needed {17b}

After the completion of the analysis of primary and secondary outcomes, the identities of the two groups will be unveiled.

## Data collection and management

### Plans for assessment and collection of outcomes {18a}

The primary outcome data will be evaluated at baseline, after 2 months of treatment, and after 4 months of treatment. Secondary outcomes, which encompass additional rating scales and hdEEG, will likewise be assessed at baseline, after 2 months of treatment, and after 4 months of treatment. Furthermore, secondary outcomes, such as fMRI, will be acquired at the baseline and upon completion of the treatment. All variables outlined in the protocol will be meticulously recorded within an encrypted Microsoft Office Excel document. The investigators responsible for data entry in this Office Excel file hold the duty of upholding data accuracy and completeness. To supervise and administer the trial data, a management team has been established, composed of the principal investigator, senior investigator, a research assistant, and a doctorate student each with their respective responsibilities for tasks.

### Plans to promote participant retention and complete follow-up {18b}

Patients will be required to participate in all evaluations and treatments over the course of the 4-month trial. The patients will be provided with trial-related assessments, such as rating scales and medical examinations, which will include ultrasound examinations, hdEEG, and fMRI, without incurring any financial expenses or burdens.

If a participant chooses to discontinue their involvement in the study during the therapy phase and fails to complete the entire 4-month treatment duration, their data will not be maintained for the purpose of analysis. It is imperative to exert all conceivable efforts in order to incentivize and provide assistance to patients, ensuring their sustained participation in the study until the completion of their intended outcome assessments.

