### Data management {19}

Clinical data will be collected and managed using an electronic database during participants’ hospital visits at baseline, 2 months, and 4 months (Table 1). The paper version materials, which include the protocol, case reported forms, informed consent forms, and electronic version database, will be kept in an independently secured box at Shanghai Sixth People’s Hospital by the principal investigator. The research assistants will send out reminder emails and make phone calls to ensure that participants complete the research. If (1) the participant withdraws his or her consent and (2) exclusion criteria are discovered after registration, the participant will be removed from the study. The reason for the suspension as well as the date of the suspension will be documented. The consent form will include permission to utilize data collected prior to the participant’s withdrawal.

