## Statistical methods

### Statistical methods for primary and secondary outcomes {20a}

SPSS 26.0 will be used for the statistical analysis. Continuous variables will be represented by a mean and standard deviation, whereas categorical variables will be represented by counts and percentages. The intention-to-treat principle will be used to analyze the UPDRS III score (primary outcome) [37], which will include data from all randomized individuals. A per-protocol analysis of other outcomes from the participants who completed the entire research will also be performed. Multiple imputations will be used to replace missing data using multivariable regression models with chained equations. The mean treatment differences and 95% CIs between measures with LIPUS and sham-LIPUS will be computed. All statistical tests will be two-sided with a *p* < 0.05 statistical significance level.

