### Methods in analysis to handle protocol non-adherence and any statistical methods to handle missing data {20c}

To mitigate protocol non-adherence, participant education will place significant emphasis on the importance of adhering to the protocol. Meanwhile, investigators and research staff will receive comprehensive training and ongoing support. Furthermore, a WeChat group will be established for each participant. Within this group, daily treatment photos will be shared to facilitate supervision and identification of stimulation sites.

We anticipate minimal missing data in the outcome (rating scale) assessments, as we have provisions in place to assess participants remotely using a dedicated mobile application in the event that they are unable to visit the hospital during the treatment phase. Missing data will be imputed using the last observation carried forward (LOCF) analysis.

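### The plan promises intention-to-treat on all randomised participants but also says data from those who choose to leave before 4 months will not be kept for analysis; the primary analysis set is contradictory

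*Protocol article*

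**What the plan says.** Four statements in the protocol article bear on who is analysed.

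- **Statistical methods {20a}.** UPDRS III is analysed by intention-to-treat, "which will include data from all randomized individuals". For the remaining outcomes: "A per-protocol analysis of other outcomes from the participants who completed the entire research will also be performed". On gaps in the data: "Multiple imputations will be used to replace missing data using multivariable regression models with chained equations".
- **Participant retention {18b}.** Where a participant chooses to end their involvement during the therapy phase and "fails to complete the entire 4-month treatment duration, their data will not be maintained for the purpose of analysis".
- **Data management {19}.** Consent withdrawal is one ground for removal; the other reads "exclusion criteria are discovered after registration, the participant will be removed from the study". The same section adds: "The consent form will include permission to utilize data collected prior to" the participant's withdrawal.
- **Non-adherence and missing data {20c}.** "Missing data will be imputed using the last observation carried forward (LOCF) analysis".

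The sample size section ({14}) allows for 10% dropout and a total of 48.

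**The concern.** Take a randomised participant who is assessed at 2 months and chooses to leave at month 3. Under {20a} they belong in the primary analysis. Under {18b} their data are not kept for it. The analyst must break one rule, and the choice could be made after the data have been seen.

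The treatment is a 30-minute session at home every day for 4 months. Leaving may plausibly depend on lack of benefit or poor tolerability, and therefore on arm and outcome. Excluding leavers after randomisation then compares groups that randomisation no longer balances. It also discards any 2-month score a leaver contributed. Both imputation methods named in the article would draw on that score.

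**Working it through.** **1. The rules side by side.** {20a} defines the set by randomisation. {18b} defines it by completion, and it speaks of analysis explicitly. {19} secures permission to use data gathered before withdrawal, so consent does not require the discard. No sentence ranks these rules.

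**2. The plan's own figures.** Inputs from {14}: changes of 5.54 (SD 8.03) and −0.71 (SD 2.25), two-sided alpha 0.05, 90% power, 10% dropout. The difference is 5.54 − (−0.71) = 6.25.

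Method: unequal-variance t-test with the noncentral t distribution.
- SE = √[(8.03² + 2.25²)/n] = √(69.54/n)
- df = (n − 1)(8.03² + 2.25²)²/(8.03⁴ + 2.25⁴)
- noncentrality = difference/SE

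| n per arm | Difference | SE | df | Noncentrality | Power |
|---|---|---|---|---|---|
| 20 | 6.25 | 1.865 | 21.97 | 3.352 | 0.893 |
| 21 | 6.25 | 1.820 | 23.12 | 3.434 | 0.908 |
| 24 | 5 | 1.702 | 26.59 | 2.937 | 0.8078 |
| 22 | 5 | 1.778 | 24.28 | 2.812 | 0.770 |
| 21 | 5 | 1.820 | 23.12 | 2.748 | 0.749 |

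So 21 per arm is the smallest n reaching 90%, 21/0.9 = 23.3 rounds up to 24, and 2 × 24 = 48. All stated figures reproduce. The 0.8078 is obtained only with 24 per arm analysed. With the plan's own evaluable target of 21 it is 0.749.

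**3. How many could be lost.** 48 × 0.10 = 4.8, about 5 participants, or 2 to 3 per arm if spread evenly.

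**4. Possible bias.** This is a simulation under assumptions the article does not supply: no true effect, 24 per arm, normal changes with higher values better, Welch test, and 2 of 24 LIPUS participants deleted with none from sham. Leaving is tied to outcome by a correlation; a value of 1 means the 2 worst leave.

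| Correlation of leaving with outcome | SDs 8.03 and 2.25: bias, type I error | Common SD 5.90: bias, type I error |
|---|---|---|
| 0.3 | 0.37 points, 5.6% | 0.28 points, 5.3% |
| 0.5 | 0.63 points, 6.8% | 0.47 points, 6.0% |
| 1 (worst case) | about 1.3 points, about 14% | 0.93 points, about 10% |

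With only 1 LIPUS participant deleted in the worst case, at SDs 8.03 and 2.25, bias is about 0.7 points and type I error about 8%.

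**The case against.** The best defence is that {20a} is the statistical section and should prevail, with {18b} being loose wording about retention. That is a reasonable guess at intent, but the article does not say so. Nor does condensation for a journal explain the conflict, because both rules are stated outright.

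The defence does block several stronger readings that a reader might infer:

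- **That the primary analysis is a completer analysis.** This follows only if {18b} overrides {20a}, which is not stated.
- **That everyone who stops treatment early is deleted.** {18b} concerns those who choose to leave the study. It does not clearly reach discontinuation for a serious adverse event, which {11b} lists as a separate ground, or someone who stops the device but stays in follow-up.
- **That participants found ineligible late are deleted from analysis.** {19} speaks of removal from the study, joins its two conditions with an and, and in the same section permits use of earlier data. This is ambiguous, not an order to delete.
- **That secondary outcomes are analysed only in completers.** {20a} says the per-protocol analysis will also be done. No other set is named for these outcomes, so the restriction is possible but not stated.
- **That adverse events of leavers are lost.** {22} says all adverse events during the trial will be documented, and {18b} does not mention safety data.
- **That imputation has nothing left to do.** Participants who stay but miss an assessment would still need it.

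The 14% figure is also extreme. It assumes that leaving tracks outcome perfectly, occurs only in the LIPUS arm, and that very unequal SDs coexist with no effect. With a common SD and the 2 worst deleted from each arm, bias is zero and type I error about 7.5%.

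**Conclusion.** The contradiction on the primary analysis set is real and explicit, and it should be resolved before the groups are unblinded. It does not call the sample size into question.

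If the discard rule is applied at the planned dropout, power for 5 points falls from 0.8078 to about 0.75 with 21 analysed per arm. The bias depends on why people leave. It is about 0.4 to 0.6 points, with type I error of 6 to 7%, under the assumed correlations of 0.3 to 0.5 and the plan's SDs. The upper bound is about 1.3 points and 14%. If leaving is unrelated to outcome there is no bias, only lost precision.

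Keeping leavers in the set does not by itself restore 0.8078, because that figure assumes 24 observed outcomes per arm. It does remove selection by completion from the primary comparison.

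**What to change.** - Delete the discard rule in {18b}.
- State in {20a} that all randomised participants stay in the primary UPDRS III analysis by assigned arm, using all data collected before withdrawal, as the consent provision in {19} permits.
- Clarify in {19} that removal from the study does not mean removal from the primary analysis set.
- State that secondary outcomes are also analysed in all randomised participants, with the completer analysis as a sensitivity analysis.
- State that adverse events are reported for everyone who started the device, including those who leave.
- Where follow-up is still open and consent remains, use the 2- and 4-month visits already scheduled for participants who stop the device.

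The cost is protocol wording, ethics approval of the change (which {25} requires) and a little more analysis, with no extra participants or visits. The last item may no longer be possible: the trial status section expected the last visit in February 2024 and the article appeared in April 2024. The other items do not depend on further visits, provided the leavers' records have been retained, which the sponsor should confirm.
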